## Abstract

**Background:**

A growing body of evidence has demonstrated that a gender-sensitive approach to healthcare is needed in all areas of medicine. Although medical and nursing guidelines include gender-sensitive care (GSC+) recommendations, the level of implementation in health care practice is unknown. This study aims to examine the current level of implementation and acceptance of GSC+ among physicians and nurses and to identify potential gaps between guidelines and practice and barriers and facilitators of GSC+ implementation, taking the perceptions of all relevant stakeholders into account. The overarching aim is to develop holistic recommended actions to strengthen GSC+.

**Methods:**

This study has a mixed methods triangulation design. The preparation phase consisting of a literature review and a two-part (qualitative and quantitative) data analysis will be conducted in the cardiology department of 9 pilot hospitals in Berlin, North Rhine-Westphalia, Lower Saxony, Rhineland-Palatinate, Germany. 18 focus groups with clinicians and nurses as well as interviews with experts in other relevant fields will be performed. In the national roll-out phase, a questionnaire survey will be conducted with hospital clinicians (n = 382), nurses (n = 386) and patients (n = 388).

**Discussion:**

This study will provide comprehensive insights into the implementation and acceptance of GSC+ in cardiology from the perspective of doctors, nurses, patients, stakeholders and experts in relevant fields, such as policy and education. A focus will also be on the extent to which age or gender of health professionals, region and hospital type influence the implementation of GSC+. The identification of GSC+ implementation barriers and facilitators should help to improve the standard of care for cardiology patients of all genders. The outcomes from this study can be used to develop measures and recommended actions for the successful and sustainable implementation of gender-sensitive care.

**Trial registration:**

The study is registered in the German Register of Clinical Studies (DRKS) under study number DRKS00031317.

## Introduction and background

A growing body of evidence has demonstrated the need for gender-sensitive care (GSC+) in all medical specialties. Gender-sensitive care plus considers the care on “sex”—the different biological and physiological characteristics of females and males and “gender”–the socially constructed characteristics of women and men [1] and further “factors of diversity”–age, sociocultural and socioeconomic status, social support / nursing work, mental health, physical performance, religion / worldview, ethnicity and sexual identity. For myocardial infarction (MI), in-hospital lethality is still significantly higher in women than in men. Medical guidelines and nursing expert standards include recommendations for gender-sensitive care, but it is unknown how these are implemented in health care practice. It is hypothesized that there is a discrepancy between evidence-based GSC+ guidelines and expert standards and their implementation in practice. Possible reasons include lack of knowledge, acceptance, or routine use of GSC+ by health care providers. Evidence also suggests that recommendations at the medical level need to be supported by guidelines at the policy level if they are to be successfully implemented. Gender-sensitive care recommendations are intended to improve the quality of health care and to achieve gender equality and more patient-centered care [1–3].

Gender medicine has its historical roots in the USA and originated in the field of cardiology [4]. The importance of sex- and gender-sensitive medicine was recognized in Germany in the 1970s. During the second wave of the women’s movement in the 1970s and 1980s, gender equality and women’s rights to control over their bodies and reproductive rights were demanded. In the later course of the feminist movement, other neglected issues such as pathologies occurring during pregnancy and childbirth or gender differences in heart disease were increasingly addressed [5].

Initially, gender-sensitive care was approached mainly from a medical perspective without considering the nursing perspective. Even today, studies on gender-sensitive care in nursing are scarce and further research is needed [2, 3]. Patient care in hospitals is a holistic synergy between medicine and nursing. With the exception of the DNQP’s "Expert Standard for the Promotion of Urinary Continence in Nursing", German expert standards rarely include recommendations for GSC+ in nursing. The German Expert Standards, developed by the German Network for Quality Development in Nursing (Deutsches Netzwerk für Qualitätsentwicklung in der Pflege (DNQP)), aim to ensure quality in all areas of health care. They are divided into three areas: structural quality, process quality, and outcome quality. According to §113 of Social Security Code XI (SGB XI), their realization and implementation is mandatory for every nurse. Overall, gender-sensitive nursing is a young science, and only a few studies on the implementation of gender-specific nursing have been published [3, 4]. The recent Covid-19 pandemic drew increased attention to the differential impact of the disease on women and men. Support from the media promoted public awareness of the need for gender-sensitive care and research in several specialties.

Until the 2000s, clinical research predominantly utilized white men with a weight of 70 kg and a height of 180 cm as the standard [5]. The thalomide scandal in the 1960s, among others, led to an increased awareness of the need to include women in (pharmacological) research [5]. Eventually, it became a legal requirement to include women in clinical trials. Since 2014 the regulation on clinical trials (REGULATION (EU) No 536/2014 OF THE EUROPEAN PARLIAMENT AND OF THE COUNCIL of 16 April 2014 on clinical trials on medicinal products for human use, and repealing Directive 2001/20/EC) states, that the participants in the trial group should be representative of the population to be treated. In terms of research and trials, this means equal representation of women and men. However, the database of most studies is gender biased.

From a medical perspective, it is well known that appropriate consideration of gender-sensitive characteristics is indispensable for adequate patient-oriented and individualized care. Sex and gender influence the symptoms and course of disease [6]. Consequently, gender-sensitive evidence-based practice (EBP) is included in medical guidelines for several medical specialties in many different countries [7].

Cardiology is the specialty with the longest history of gender-sensitive health care research. Coronary heart disease is the most commonly diagnosed cardiovascular disease (CVD). MI is the leading cause of death in Germany [12, 13]. There is considerable evidence that the symptoms of myocardial infarction differ significantly between men and women. While men are more likely to present with left chest pain and dyspnea (the "classic" symptoms of MI), women are more likely to present with non-specific symptoms (e.g., nausea, vomiting, and dizziness) [14]. Consequently, women die more frequently in the hospital from MI than men [15, 16].

To ensure gender equality in medicine and nursing, health professionals should follow the relevant medical guidelines and nursing expert standards. In Germany, cardiologists should follow the guidelines of the European Society of Cardiology (ESC), the German Society of Cardiology–Cardiovascular Disease Research (Deutsche Gesellschaft für Kardiologie—Herz- und Kreislaufforschung e.V. (DGK)), and the Association of the Scientific Medical Societies (Arbeitsgemeinschaft der Wissenschaftlichen Medizinischen Fachgesellschaften (AWMF)). Nurses should follow the "Expert Standards" of the German Network for Quality Development in Nursing (Deutsches Netzwerk für Qualitätsentwicklung in der Pflege (DNQP)).

Numerous studies have shown differences in diagnostic and treatment outcomes between women and men [8]. Several reasons for these gender disparities and failures of implementation in health care are known [9–11]. In health care interest in the implementation of gender-sensitive care has increased [12]. According to Celik et al. [13], the successful implementation of gender sensitivity in health care practice requires the use of a multi-pronged approach that includes the professional, organizational and political insight needed to identify barriers and facilitators and to develop measures and recommendations. Other dimensions such as education, technology, sponsorship, and politics must also be taken into account.

This study of the implementation and acceptance of gender-sensitive care in cardiology in German hospitals from the perspective of clinicians, nurses, patients and other stakeholders and experts aims to provide evidence-based research findings on this topic.

### Hypotheses

The main objectives of the study HeartGap are to investigate the current level of implementation of gender-sensitive care in cardiology, to determine whether there is a discrepancy between existing evidence from guidelines and nursing expert standards and health care practice. Furthermore, the acceptance of GSC+ by clinicians and nurses will be examined. Evidence-based medical guidelines and expert standards are important tools and frameworks for the holistic implementation of medical knowledge and high-quality health care.

The following hypotheses will be evaluated in this study:

The translation of theoretical knowledge about gender-sensitive care (status of guidelines and expert standards) cannot be implemented sufficiently into health care practice due to a knowledge deficit (target state ≠ actual state).The working conditions (staff shortages and budget pressures) are decisive factors for the low level of implementation of gender-sensitive care.There is a lack of sufficient knowledge about the GSC+ requirements formulated in medical guidelines and expert standards.The gender-sensitive care requirements formulated in medical guidelines and expert standards are incompatible with everyday care practice.The gender-sensitive care requirements formulated in medical guidelines and expert standards do not correspond to the attitudes of health care professionals.Aspects such as the age and professional experience of health care professionals and gender as well as the type of hospital and the size of the region can have an influence on the implementation of GSC+.

In summary, the HeartGap study aims to comprehensively assess the situation of GSC+ in cardiology and to investigate the correspondence between existing guidelines, expert standards and actual practice of care. The hypotheses of the study examine potential barriers, including knowledge deficits, working conditions and compatibility problems between the formulated requirements in guidelines and expert standards and daily care routines. In addition, the study recognizes the importance of contextual factors, such as nurse and physician demographics, hospital type and regional size, to the successful implementation of gender-sensitive care. Through this multi-faceted investigation, the study aims to provide valuable insights for better integration of GSC+ into cardiovascular healthcare practice.

## Methods and design

### Aim

The overarching aim of this study is to provide insight into the current level of implementation of GSC+ and guidelines for clinicians and expert standards and the willingness to implement GSC+ guidelines in practice in the German hospital sector. The study purposes to answer the research questions described below.

### Main research question

Is the content of evidence-based gender-sensitive care guidelines for clinicians and expert standards being implemented in care practice and, if so, to what extent?

### Secondary research questions

What are the current deficits in the implementation of GSC+ in cardiology from the perspective of clinicians, nurses and patients?What are the barriers and facilitators to the implementation of GSC+ in cardiology (e.g., workload, process factors, compensation systems, ignorance or uncertainty)?Which measures promote the implementation of GSC+ in cardiology?

### Theoretical background: Roadmap for implementation

In order to cover all relevant aspects, a theoretical framework is used for the analysis. Moise et al. [14] published a statement on behalf of the American Heart Association Council on Epidemiology and Prevention, Council on Hypertension, and Stroke Council entitled "Leveraging Implementation Science for Cardiovascular Health Equity". The authors break down the implementation of EBPs shown to promote CVD equity into four steps:

Step 1. Select and adapt EBPs.Step 2. Identify barriers and facilitators to implementing EBPs for (CVD) equity.Step 3. Select, use and adapt implementation strategies.Step 4. Evaluate implementation success.

For this specific study setting, the above roadmap was adapted to create an individualized roadmap consisting of the following 5 steps:

Screening of medical guidelines and expert standards for gender-sensitive aspects.Developing of indicators from selected gender-sensitive aspects, which are reviewed in practice by the quantitative survey.Identifying barriers, facilitators and measures by a scoping review, which are relevant to the implementation of GSC+ in CVD.Empirical qualitative and quantitative analysis to answer the research questions and test the hypotheses.Triangulation of the data to derive recommendations for GSC+ implementation.

An evaluation of implementation success (step 4 of Moise et al.’s roadmap) will not be performed in the scope of this health care research study.

### Design

This mixed methods-triangulation study includes a scoping review as well as a quantitative and qualitative analysis of the data to examine the research topic from different perspectives (Fig 1).

Analysis of the gap between expectations (medical guidelines and expert standards) and the current implementation by hospital physicians and nurses in practice.Identification of facilitators and barriers to the implementation of gender-sensitive care.Development of measures and recommended actions to improve the implementation of gender-sensitive care in practice.

**Fig 1 pone.0301732.g001:**
[figure not shown]
Linkage of methods and research questions. Fig 1 shows the correlation between the central research questions and the methods used to address them in this study.

In the preparation phase, the ESC guidelines and the national Association of the Scientific Medical Societies e.V.(AWMF) and (German Cardiac Society) DGK guidelines for cardiology and the DNQP expert standards for nursing were screened for GSC+ recommendations. Based on these guidelines, indicators will be developed to assess the level of implementation of gender-sensitive care. Gender-sensitive aspects of the patient pathway from admission to diagnosis, treatment and discharge will be analyzed. The implementation of these criteria will be reviewed in the course of the empirical research. The qualitative analysis will include focus group interviews conducted in 9 nationally selected pilot hospitals in separate groups of 5–7 nurses and clinicians. In addition, individual interviews will be conducted with experts from the medical and nursing professions, as well as with policymakers and other relevant stakeholders. The quantitative analysis will include questionnaire surveys that will be conducted via a nationwide roll-out including clinicians, nurses and patients.

The individual survey elements are interdependent, which means that the results of the previous part of the survey will determine the design of the following part. The elements are described in detail below.

### Setting

The HeartGap study will be conducted prospectively in the German states of Berlin, North Rhine-Westphalia, Lower Saxony, Rhineland-Palatinate. Data will be collected from these states to achieve a representative national sample including eastern and western German states, a city state, large and medium-sized cities, and a rural community. As shown in Table 1 (Attributes (number of inhabitants and grade of care) utilized as parameters to calculate stratified random sample), the study areas will be divided into three categories according to population size (large cities with more than 100,000 inhabitants, cities with 5,000 to 100,000 inhabitants, and rural communities with less than 5,000 inhabitants), and the hospitals will be divided into four categories according to level of care, defined as the number of hospital beds (teaching and research hospital with >800 beds, large hospital with > 800 beds, medium-sized hospital with 501 to 800 beds, and small hospital with ≤500 beds) (Table 1). In Germany, the classification of hospitals into care levels is based on the number of beds, which is why this classification was adopted in the course of the study. Focus groups from each level of care will be conducted in 3 regional categories. Each focus group will consist of either physicians or nurses. In the rural region, focus group interviews will be conducted in a hospital with less than 500 beds due to the lack of larger hospitals.

**Table 1 pone.0301732.t001:** Attributes (number of inhabitants and grade of care) utilized as parameters to calculate stratified random sample.

Level of care -------------------- Population size	Teaching / research hospital with > 800 beds	Hospital with > 800 beds	Hospital with 501–800 beds	Hospital with ≤ 500 beds
Large city (≥ 100,000 inhabitants)				
City (5,000 to 99,000 inhabitants)				
Rural community (< 5,000 inhabitants)	*Hospitals in this stratum do not exist in Germany*	*Hospitals in this stratum do not exist in Germany*	*Hospitals in this stratum do not exist in Germany*	

Table 1 illustrates how the attributes of the number of inhabitants in a region and the nursing degree of a hospital were combined as parameters for the calculation of the stratified sample.

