#### Quantitative survey

An a-priori sample size calculation was conducted to determine the number of cases needed. First, the number of participating clinicians, nurses and inpatients with CVD disease in cardiology and internal medicine wards was recorded. Therefore, the data of the German Hospital Quality Recording System were used. Samples were calculated using WINPEPI software according to the attribute grid (Table 1). According to our sample size calculations (Study aim: estimating a mean–stratified random sample, confidence level: 0.95, acceptable difference: 0.05 and number of strata: 9) based on the Cochran formula [15], 382 clinicians, 386 nurses and 388 cardiology patients must be included in the quantitative study during the 2-year study period (January 2023 to December 2024). WINPEPI shows the weighting per strata of how many people are to be recruited.

Utilizing pre-established connections from the qualitative investigation and the extensive network of the project consortium, facilitates the engagement with hospitals for the quantitative phase. To ensure comprehensive representation, the stratification framework developed for the qualitative study is used to include care providers from hospitals of different care levels and geographical regions. Inclusion criteria for cardiologists and nurses are, that they currently work on a cardiology ward setting, other factors such as migration are not taken into consideration in the selection of participants. In addition to the age and gender of the caregivers, the survey also asks whether the person was born in Germany in order to determine the influence of other diversity factors such as migration background. In the healthcare sector, a very high proportion of employees have a migration background, accounting for approximately 25% of all employees [16]. Therefore, the study also aims to investigate whether this aspect influences gender-sensitivity or knowledge.

For participants (physicians, nurses and patients) in the quantitative survey, the recruitment period is from October 1, 2023 to June 30, 2024. The nine pilot hospitals and further hospitals in Germany (on average four hospitals per strata are needed) are to recruit to reach the calculated sample size.

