### Quantitative data collection and analysis

Following the literature review and qualitative data analysis, questionnaires for quantitative data collection and analysis will be designed for patients and healthcare providers (clinicians and nurses). The aim is to determine the level of gender-sensitive care and to review the respondents’ knowledge and acceptance regarding the content on GSC+ in medical guidelines and expert standards (hypothesis 1). The healthcare provider questionnaire will focus on transfer of medical guidelines and expert standards in routine practice. The patient questionnaire will focus on the patient’s perception of sex and gender in the care process. The aim of the patient survey is to investigate: What needs do patients have with regard to gender-sensitive care and whether their ideas coincide with those of care providers. To collect representative data of professionals and patients, a national roll-out of the study at various hospitals in Germany is planned, and factors such as level of care and location of the hospital and socio demographic factors such as sex and age will be analyzed. The analysis is based on personal characteristics such as sex, age, education and vocational training and migration background.

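### The survey is labelled stratified random and nationally representative, but the only hospital selection described runs through pilot contacts and the consortium network, and its geographic frame is contradictory

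*Protocol article*

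**What the plan says.** **The claim.** The Setting section says the study is "conducted prospectively in the German states of Berlin, North Rhine-Westphalia, Lower Saxony, Rhineland-Palatinate", and continues: "Data will be collected from these states to achieve a representative national sample including eastern and western German states". The title of Table 1 presents its grid of population size by level of care as the basis of a stratified random sample. Recruitment, Quantitative survey, gives the inputs of the size calculation as "Study aim: estimating a mean–stratified random sample, confidence level: 0.95, acceptable difference: 0.05 and number of strata: 9". The result is stated as "based on the Cochran formula [15], 382 clinicians, 386 nurses and 388 cardiology patients must be included". Quantitative data collection and analysis again promises representative data on professionals and patients.

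**The selection.** Recruitment, Quantitative survey, describes how survey hospitals are reached: "Utilizing pre-established connections from the qualitative investigation and the extensive network of the project consortium" is said to ease engagement with hospitals. The stratification framework from the qualitative study is used so that different care levels and regions are covered. The survey sites are the nine pilot hospitals plus further German hospitals, at an average of four per stratum.

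**The geography.** The Abstract attaches the four states to the nine pilot hospitals and places the survey in a separate national phase. The Design section calls the survey nationwide. Quantitative data collection and analysis says "a national roll-out of the study at various hospitals in Germany is planned".

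**The concern.** The main research question asks to what extent guideline content is implemented. That is an estimate of a level, so its value depends on which population the respondents stand for. A 95% interval with half-width 0.05 has its stated meaning only if respondents are drawn by a known chance mechanism from the named population. The article asserts such a mechanism in its label and its sample size, but describes contact-based access to hospitals and the filling of strata.

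If hospitals that are easy to reach differ from the rest in how they implement gender-sensitive care, the estimate is shifted by an amount that the interval does not show and that more respondents do not reduce. The reader also cannot tell whether the target population is Germany or four states.

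**Working it through.** **1. Reproduce the stated sample size.** Inputs from the article: confidence 0.95 (z = 1.96), acceptable difference d = 0.05, Cochran formula. The standard deviation is not given; I assume 0.5, that of a proportion near one half.

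n = (z × SD / d)² = (1.96 × 0.5 / 0.05)² ≈ 384.1, rounded up to 385.

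The stated 382, 386 and 388 all lie within 3% of this. A finite-population correction gives about 382 for an assumed population of 70,000, and rounding up within strata could explain 386 and 388. The number of strata also agrees: 3 × 4 cells less 3 empty rural cells = 9. The arithmetic is not at fault.

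**2. Compare the assumption with the described selection.**

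| Needed for the stated precision | What the article describes |
|---|---|
| One defined population | Four states (Setting); Germany (Abstract, Design, Recruitment, Quantitative data collection and analysis) |
| A chance draw within each stratum | Contacts from the qualitative study and the consortium network; strata used to cover hospital types |
| Known selection probabilities | A required number per stratum, with no draw of hospitals, staff or patients stated |

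A target count per stratum fixes how many respondents come from each cell, not which ones. Without a draw, that is quota filling.

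**3. How large a part the pilot hospitals form.** Nine strata at an average of four hospitals give about 36. If that average includes the pilots, they are 9/36 = 25% of the sites. The nine pilots are included by design. Their staff are approached for focus groups on the survey's own subject between March and December 2023, and survey recruitment starts in October 2023. How many of the other hospitals would come through the network is not stated.

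**4. What an undetected bias would do (illustration only).** At n = 384 with SD 0.5, the standard error is 0.5 / √384 = 0.0255. For a bias b, the coverage of the nominal 95% interval is Φ(1.96 − b/SE) − Φ(−1.96 − b/SE).

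| Assumed bias b | b/SE | Actual coverage |
|---|---|---|
| 0.0125 | 0.49 | 0.92 |
| 0.025 | 0.98 | 0.835 |
| 0.05 | 1.96 | 0.50 |

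These values of b are not taken from the article and are not estimates of the bias here. They show that a shift no larger than the plan's own acceptable difference is enough to make the 95% statement untrue.

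**The case against.** **The article is condensed.** A draw within strata may be described in a fuller protocol, and contacts that ease engagement do not strictly exclude one. The pilot hospitals were identified through the stratification and then approached by email and telephone, so they are not shown to be earlier acquaintances of the consortium. This stands as a caution, and it is why the point asks for the draw to be described or the label changed. It does not remove the point, because the article itself puts the random and representative labels beside a contact-based route.

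**The survey is nationwide.** A reader might infer from the Setting section that survey data come only from four states. The documents do not support that as a settled fact: four other places describe a national survey. What stands is a contradiction to be reconciled.

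**East and west.** Because the Setting section speaks of eastern and western states, a reader might infer a flawed east–west comparison. That factor is not in the stratification grid, the hypotheses name hospital type and size of region, and no such comparison is planned.

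**Direction of bias.** A reader might infer that network hospitals implement gender-sensitive care better, so that the level will be overestimated. The article does not describe the network's hospitals in a way that shows this.

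**Conclusion.** The point holds as a mismatch between label and method. The article claims a stratified random, nationally representative sample with 0.05 precision, and describes a stratified non-probability sample of participating hospitals. The sample sizes follow from the stated formula (with SD 0.5 assumed), but the precision and the national inference do not follow from the selection described. The frame is stated in two incompatible ways.

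No figure for the bias can be given: the documents supply neither the share of respondents reached through contacts nor any difference between those hospitals and others. The conclusion rests on the article's text alone and would fall away if a probability draw from one stated frame were documented.

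**What to change.** 1. **State one survey frame.** If it is Germany, limit the four-state sentence in the Setting section to the pilot hospitals.
2. **Then choose one of two routes.**
   - *Draw.* Select the further hospitals at random within each of the nine strata, using the hospital quality-record data already used for the counts. This assumes those data identify hospitals by stratum. Flag pilot and network hospitals in the data set, and report the main estimates with and without them. The precision should then be restated for clustering. With 36 hospitals and 382 clinicians there are 382/36 = 10.6 per hospital. An assumed intraclass correlation of 0.01 to 0.10 gives a design effect, 1 + 9.6 × ICC, of 1.10 to 1.96 and a half-width of about 0.052 to 0.070.
   - *Relabel.* If no draw is made, replace the random and nationally representative labels with *stratified non-probability sample of participating hospitals*, present the 0.05 precision as nominal only, and limit the conclusions to those hospitals.

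**Cost.** The first route needs a random ordering of existing data, one flag variable and one sensitivity estimate; its downside is more refusals from hospitals without prior contact. The second needs only wording; its downside is a more modest claim.
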